# Acupuncture in diabetic peripheral neuropathy—protocol for the randomized, multicenter ACUDPN trial

**DOI:** 10.1186/s13063-021-05110-1

**Published:** 2021-02-26

**Keywords:** Acupuncture, Chinese medicine, Peripheral neuropathy, Type II diabetes mellitus, Complementary medicine, Randomized controlled trial

## Abstract

**Background:**

Acupuncture is used to treat patients with diabetic peripheral neuropathy; however, the evidence is unclear. We present the design and methodology of the ACUDPN (ACUpuncture in Diabetic Peripheral Neuropathy) trial, which investigates the effectiveness of acupuncture for the treatment of diabetic peripheral neuropathy (DPN) symptoms. The aim of this study is to investigate whether acupuncture is effective for the treatment of DPN symptoms.

**Methods:**

This study is a two-armed, randomized, controlled, parallel group, open-label, confirmatory, multicenter trial (8-week intervention period plus 16 weeks of follow-up). Physicians in outpatient units in Germany who specialize in acupuncture treatment will treat 110 diabetes type II patients with clinical symptoms of peripheral neuropathy in the feet and legs with signs of neuropathy according to nerve conduction testing. The patients will be randomized in a 1:1 ratio to one of the following two groups: (a) semi-standardized acupuncture plus routine care or (b) routine care alone. Acupuncture will consist of 12 treatments per patient over 8 weeks. The primary outcome will be the overall DPN-related complaints in the extremities after 8 weeks as measured by the Visual Analog Scale (VAS). Further outcome measures will include DPN-related pain, the Neuropathic Pain Symptom Inventory (NPSI), Diabetic Peripheral Neuropathic Pain Impact (DPNPI) scores, and nerve conduction parameters of the sural nerve at weeks 8, 16, and 24.

**Discussion:**

The results of this trial will be available in 2021 and will help clarify whether acupuncture can be considered effective for the treatment of DPN with regard to the subdimensions of the neuropathic clinical picture.

**Trial registration:**

ClinicalTrials.gov NCT03755960. Registered on 11 August 2018.

**Supplementary Information:**

The online version contains supplementary material available at 10.1186/s13063-021-05110-1.

## Administrative information

Note: The numbers shown in curly brackets in this protocol refer to Additional file 1 item numbers. The order of the items was modified to group similar items (see http://www.equator-network.org/reporting-guidelines/spirit-2013-statement-defining-standard-protocol-items-for-clinical-trials/).

**Table Taba:** 

Title {1}	Acupuncture in Diabetic Peripheral Neuropathy - Protocol for the Randomized, Multicenter ACUDPN Trial.
Trial registration {2a and 2b}.	ClinicalTrials.gov: NCT03755960. First registered on 11.28.2018
Protocol version {3}	Version 1.0_22102018
Funding {4}	Investigator-initiated trial. University Medicine Charité Berlin. Partially financed by [name] research grant from the Veronica and Karl Carstens Foundation.

## Background and rationale {6a}

Approximately 14–30% of all diabetic patients in Germany are affected by sensorimotor neuropathy [1]. Furthermore, neuropathy has been related to impaired glucose tolerance and can appear before the onset of diabetes [2].

In addition to chronic discomfort or pain, the destruction of nerve fibers can lead to the complete loss of sensation in the feet and legs, which increases the risk of diabetic foot syndrome [3]. Minor plantar cuts and trauma are overlooked and remain untreated. Due to a concomitant impairment in vascularization, wounds do not heal well, and surgical interventions as invasive as repeated amputations can become necessary [4]. Diabetic foot syndrome has dermatological, atherosclerotic, and orthopedic dimensions, and in 85–90% of cases, sensorimotor peripheral and distal symmetric neuropathy is present [5].

The authors of a Cochrane meta-analysis concluded that even strict management of blood sugar levels could not reverse or stop the destruction of nerve fibers in type II diabetes [6]. Thus far, only symptomatic treatment has been implemented for DPN [7]. The pharmacological approach for paresthesia or the painful symptoms of DPN consists of analgesics, including anticonvulsants and antidepressants, such as amitriptyline, duloxetine, pregabalin, gabapentin, and opioids. The reduction in DPN symptoms with the help of these pharmaceuticals has been reported to be insufficient due to the lack of alleviation of numbness, and all drug options have a relevant risk of side effects and drug interactions [5], which is important for patients with metabolic syndromes who experience polypharmacy as it is also necessity to treat hypertension, hyperlipidemia, and hyperglycemia. Due to the lack of therapeutic solutions for neuropathy, an increasing number of patients are considering complementary medicine, i.e., acupuncture [8].

Acupuncture is a relatively safe treatment option that has been proven to be effective for chronic pain syndromes [9]. Chinese medicine (CM) textbooks classify neuropathies under the symptom “numbness of the four extremities”, which they explain mainly with (a) qi and blood deficiency, (b) damp heat or phlegm blocking the channels, or (c) cold that has entered the meridians. They not only contain advice regarding the symptomatic treatment of neuropathy with acupuncture but also offer a more complex solution for treating diabetic nerve destruction with a combination of dietetic and herbal prescriptions, exercise, and acupuncture [10].

Scientific evidence supporting the usefulness of such treatments in DPN remains lacking, leading to the need for well-designed clinical trials.

A systematic review involving a meta-analysis of 14 randomized controlled trials (RCTs) and 1 long-term follow-up study investigating the use of acupuncture for miscellaneous neuropathies suggests that acupuncture is effective for diabetic neuropathy, Bell’s palsy, and carpal tunnel syndrome (CTS) [11]. In 4 trials investigating diabetic neuropathy and 4 trials investigating CTS, nerve conduction studies were performed; a series of acupuncture treatments produced significantly improved effects on motor nerve function parameters in the median, ulnar, and peroneal nerves. A sensory nerve conduction study (NCS) revealed that acupuncture increased the nerve conduction velocity (NCV) in the median and peroneal nerves. In a recently published RCT, 172 patients with diabetic neuropathy received 10 acupuncture treatments or 10 laser acupuncture or 10 placebo laser treatments; sural SNAP and sural and tibial NCV improved significantly when comparing needle acupuncture to placebo [12]. Neuropathies with different etiology have been investigated in the past. In a study with a design similar to our design with a randomized waiting-list control group for effectiveness, 87 Chinese patients with chemotherapy-induced neuropathy were investigated. Within this cohort, after 8 weeks, the 10 acupuncture treatments resulted in significant clinical improvements in the primary outcome (pain), clinical neurological assessment, quality of life domains, and symptom distress [13]. A tested subset of patients had no or only borderline electrophysiological signs of neuropathy at baseline. Their parameters did not change after 8 weeks. Another small pilot study investigating chemotherapy-induced neuropathy described improved NCV parameters in 11 patients who agreed to undergo acupuncture, and the parameters were compared to those of 11 control patients who received the best medical care alone [14]. To determine whether neurophysiological changes reflect neurological rehabilitation, further well-designed controlled trials using neuropathy-specific, validated questionnaires in combination with electrophysiological data as outcome parameters are needed [15].

### Objectives {7}

The aim of this randomized controlled clinical study is to assess the effectiveness and safety of acupuncture in addition to routine care compared to routine care alone for the treatment of symptomatic DPN with respect to the postulated underlying TCM-patterns in terms of the impact on overall symptoms, pain, neurophysiological outcomes, the use of analgesics, sleep disturbances, specific and general quality of life, and adverse events.

### Trial design {8}

The ACUDPN study is a two-armed, randomized, controlled, parallel group, open-label, confirmatory, multicenter clinical trial investigating the effectiveness of acupuncture plus routine care vs. routine care alone in patients with DPN.

## Methods: participants, interventions, and outcomes

### Study setting {9}

This study is being conducted in Germany. The main recruiting center is located in Berlin at the Charité University Hospital, and another recruiting center is located in Hamburg in a research and treatment center for traditional Chinese medicine. The overall study duration per patient is 24 weeks. After randomization at baseline, the patients in the acupuncture group will undergo 12 treatment sessions in addition to routine care during the first 8 weeks of the study, followed by 16 weeks of follow-up. In the control group, all patients will continue to receive routine care and undergo several study follow-up examinations during the first 16 weeks. In this control group, patients are on a waiting list for the acupuncture treatment, which will be started at week 16 and continued until the final follow-up at week 24 using the same acupuncture treatment protocol being performed in the other study arm (see Fig. 1 and Table 1).

**Fig. 1 Fig1:**
[figure not shown]
Participant timeline {13}. Time schedule, design, and outcome parameters of the ACUDPN study. *BL*, baseline; *W8*, *W16*, etc., week 8, week 16, etc., after inclusion in the study. Outcome measures: VAS pain and VAS overall DPN-related complaints, German versions of the Neuropathic Pain Symptom Inventory (NPSI), Diabetic Peripheral Neuropathic Pain Impact (DPNPI) measure, the emotional pain perception scale (SES), the SF-12 QoL, the Patient Global Impression of Change (PGIC), and neurological exam with clinical Total Neuropathy Score (cTNS)

**Table 1 Tab1:**
[figure not shown]
Participant timeline {13}. Time schedule, design, and outcome parameters of the ACUDPN study. *BL*, baseline; *W8*, *W16*, etc., week 8, week 16, etc. after inclusion in the study. Outcome measures: VAS pain and VAS overall DPN-related complaints, German versions of the Neuropathic Pain Symptom Inventory (NPSI), Diabetic Peripheral Neuropathic Pain Impact (DPNPI) measure, the emotional pain perception scale (SES), the SF-12 QoL, the Patient Global Impression of Change (PGIC), and neurological exam with clinical Total Neuropathy Score (cTNS)

### Patients and recruitment {15}

Patients’ enrollment began in February 2019. The participants are recruited by advertisements in public transportation units and the distribution of flyers in doctors’ and podiatrists’ offices and point-of-care facilities for patients with diabetes in Berlin and Hamburg. An incentive of 50€ has been offered to physicians or podiatrist for each patient referred by their practice who could be successfully recruited for the trial.

### Eligibility criteria {10}

To participate in the study, patients must meet the following inclusion criteria: female or male patients (aged 18–80 years) with symptoms of at least moderate diabetic peripheral neuropathy, patients with a diagnosis of diabetic peripheral neuropathy due to diabetes mellitus type II, patients with minimum overall DPN-related complaints of at least 40 mm on a 0–100 mm VAS, patients with a pathological NCV < 42 m/s and/or an amplitude of the sural nerve< 6 μV, and patients who have completed titration of pain medication against DPN. In addition, patients must be able to complete a diary for the self-evaluation of symptoms, must record the use of symptomatic medication, and must provide written informed consent.

The main exclusion criteria for the patients are as follows: severe DPN with muscular weakness of the proximal leg muscles; neuropathy due to other reasons (such as borrelia infection, human immunodeficiency virus infection, hereditary factors, alcohol, or a history of neurotoxic drug use); anticoagulation or bleeding disorders; severe peripheral artery disease in Fontaine stage IV; ulcers or gangrenous lesions of the feet; severe fatigue syndrome; traumatic lesions of the nerves or vessels in the lower extremities; opioid use before inclusion in the study; regular use of cannabis or cannabinoids; lipoic acid infusions planned during participation in the trial; scheduled psychotherapy during study participation; additional therapy with complementary medicine or physical therapy for symptoms of DPN during the 6 weeks before inclusion in the study or planned during the study; obesity (BMI > 35 kg/m^2^); and pregnancy or lactation. No restrictions will be made regarding the underlying disease pattern according to the TCM diagnosis, though patterns will be registered.

### Informed consent {26a}

Written and oral informed consent will be obtained by the study’s physicians.

### Additional consent provisions for the collection and use of the participants’ data and biological specimens {26b}

On the consent form, the participants will be asked if they agree to the use of their data should they choose to withdraw from the trial. The participants will also be asked for permission allowing the research team to share relevant data with people from the universities participating in the research or regulatory authorities when relevant. This trial does not involve collecting biological specimens for storage.

### Randomization

#### Sequence generation {16a}

Individual patient randomization at a 1:1 ratio into the two study arms will be performed via a computer-generated randomization list (prepared by SAS 9.4, SAS Institute Inc., Cary, NC, USA), which will be kept at the study center in Berlin. Randomization will be stratified by the study center.

This computer-generated list shows only one result at a time and is unavailable to the enrolling study physician.

#### Concealment mechanism {16b}

Randomization is performed by the coordinating study nurse using the computer-generated randomized list (prepared by SAS 9.4, SAS Institute Inc., Cary, NC, USA); the computer reveals only one result at a time. The results of the randomization are provided via telephone to the study physician once he declares that the patient is eligible for participation.

#### Implementation {16c}

If the study physicians declare a patient eligible for enrollment, they will contact the coordinating study nurse. The nurse will generate the allocation and communicate the result to the physician via telephone and fax. Then, the physician will communicate the result of the randomization to the patient.

### Assignment of interventions: blinding {17a}

This study is an open-label study, and the participants and physicians will be aware of the treatment allocation. Only the data analysts and statisticians are blinded.

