### Procedure for unblinding if needed {17b}

The design is open label, and only the statisticians will be blinded until the end of the analysis; thus, unblinding will not occur.

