### Study intervention {11a}

Two neurologists and six examined acupuncturists (four licensed physicians with experience in TCM- research and two doctoral students with diplomas for acupuncture and 140 h of acupuncture training) are presently recruiting and treating patients. The choice of acupuncture points was made via discussion with six acupuncture experts from the following two major German societies for medical acupuncture: the German Medical Acupuncture Association (*Deutsche Ärztegesellschaft für Akupunktur*; DÄGfA), Munich, and the International Society for Chinese Medicine (*Societas Medicinae Sinensis,* SMS), Munich. The ultimate strategies were generally considered a pragmatic compromise between the need for standardization in science and the need for individualization in Chinese medicine. Furthermore, the rationale of the acupuncture- point selection was furthermore supported by the treatment strategy provided in a pilot study from Meyer-Hamme et al. [16]. The acupuncture treatment consists of 12 sessions administered over a period of 8 weeks (preferably 2 sessions in each of the first 4 weeks, followed by 1 session per week in the remaining 4 weeks). The acupuncture treatment in the ACUDPN study is semi-standardized (Table 2) as follows: all patients must be treated at the basic obligatory acupuncture points, i.e., bilaterally ST34, ST40, SP6, Ki 3, and LV3, and bilaterally at the EX-LE-10 Bafeng points, which sum up to 18 needles per session (see Fig. 2).

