### Data collection and management

#### Plans for the assessment and collection of outcomes {18a}

The baseline and follow-up neurological examinations, including the electrophysiological data collection, will be performed by two neurologists. These neurologists do not perform any acupuncture treatments. Each acupuncture treatment is documented by trained acupuncturists; the needles at mandatory and facultative points and their mode of application (i.e., stimulating or sedating technique) are noted and counted.

Medication will be listed on a medication log; any changes in pain-modifying drugs will be noted on a weekly basis in the diaries. At the baseline visit, the patients are given diaries that they take home for the first 8 weeks, and weekly outcomes are to be noted in these diaries. Every 8 weeks, via mail, the patients receive another set of questionnaires to assess the abovementioned outcomes. The diaries and questionnaires must be returned in the envelopes provided by the study center.

To prevent loss by mail, data sheets of the baseline examination are provided in duplicates; one copy remains at the study site. Upon receipt of the baseline and follow-up case report forms and the patients’ diaries and questionnaires at the main study center at the Charité University Hospital, the monitoring study staff checks for the completeness of the data. The responsible physician will be notified of any missing data from the physical or neurological evaluation within the next working day. All questionnaires and dairies are transmitted via mail; the delayed return of the questionnaires will be followed by a reminder phone call to the patient. Missing outcomes in the questionnaires will be completed by contacting the patients and sending the patients a copy of the incomplete questionnaire or isolated questions via mail.

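### The two examining neurologists give no acupuncture but are left unblinded, an avoidable risk of observer bias in the secondary outcomes NDS and cTNS

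*Protocol article*

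**What the plan says.** The section on blinding {17a} reads: "This study is an open-label study, and the participants and physicians will be aware of the treatment allocation". It continues: "Only the data analysts and statisticians are blinded". The section on unblinding {17b} repeats that "only the statisticians will be blinded until the end of the analysis; thus, unblinding will not occur".

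Under the plans for outcome assessment {18a}, "The baseline and follow-up neurological examinations, including the electrophysiological data collection, will be performed by two neurologists", and "These neurologists do not perform any acupuncture treatments".

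The Study intervention section {11a} describes the team less cleanly. It says that "Two neurologists and six examined acupuncturists" (four licensed physicians and two doctoral students make up the six) "are presently recruiting and treating patients".

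On allocation, the Concealment section {16b} states: "The results of the randomization are provided via telephone to the study physician", once that physician has declared the patient eligible. The Implementation section {16c} adds a fax and has the same physician tell the patient.

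The Outcomes section {12} lists NDS and cTNS as further secondary outcomes at baseline and weeks 8, 16 and 24.

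**The concern.** In an open-label comparison of acupuncture with a waiting list, patients and acupuncturists cannot be masked. An examiner who gives no needles can be. The plan has such examiners, yet its blinding statement is exclusive: it names analysts and statisticians and nobody else. This is a stated design choice, so it cannot be presumed that a fuller protocol or an analysis plan supplies masked assessment.

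NDS and cTNS are scored by a clinician. Unblinded patients report the primary VAS, NPSI, numbness rating, DPNPI, SES, SF-12 and PGIC. That leaves NDS, cTNS and sural nerve conduction as the efficacy measures obtained by an examiner, and so as the place where this trial could limit the influence of expectation. The Objectives section names neurophysiological outcomes, and the Discussion closes by saying the results will bear on whether acupuncture can regenerate nerves. A VAS score cannot support such a statement; it would have to rest on the neurologists' findings.

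**Working it through.** **1. The text side by side.**

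| Question | Section | Answer |
|---|---|---|
| Who knows the arm? | {17a} | Participants and physicians |
| Who is blinded? | {17a}, {17b} | Analysts and statisticians only |
| Who examines? | {18a} | Two neurologists, at baseline and follow-up |
| Do they needle? | {18a} | No |
| Do they have another role? | {11a} | Listed within a team that recruits and treats |
| Who receives the allocation? | {16b}, {16c} | The study physician who declares eligibility |

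No section provides for masked assessment. That the neurologists are unblinded follows from two words, physicians and only; they are not named in {17a}. That one of them takes the allocation call is a further inference, because four of the acupuncturists are physicians too.

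**2. Which outcomes are exposed.**

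- *NDS and cTNS:* fully exposed, since the examiner assigns the score.
- *Sural nerve conduction:* less exposed. The Outcomes section describes a 10-second device measurement giving velocity and amplitude as numbers, and the Discussion notes that no curve has to be interpreted. What remains is how a reading is taken or repeated.
- *Primary VAS:* not exposed, because the patient completes it.

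**3. Which time points.** Controls start acupuncture at week 16 (Study setting). Treated and untreated arms are therefore compared at weeks 8 and 16. By week 24 both arms have had acupuncture, and the examiner's expectation has less to act on.

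**4. The plan's sample size, used as input.** Difference 15 mm, SD 25 mm, so d = 15/25 = 0.6. A two-sided t test at 5% with 80% power needs 44.6, so 45 per arm and 90 in total (power at 45 per arm 80.4%). This reproduces the stated figure. Inflation for 15% dropout gives 90/0.85 = 105.9, so 106. The stated 110 allows for 1 − 90/110 = 18.2%, which is on the safe side.

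**5. Illustration of size.** Assume no true effect and a differential rater lean of b SD. The t statistic then has 88 degrees of freedom and noncentrality b × √(45/2) = 4.743b.

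| Assumed lean b | Noncentrality | Rejection rate, two-sided 5% test |
|---|---|---|
| 0 | 0 | 5.0% |
| 0.1 | 0.474 | 7.6% |
| 0.2 | 0.949 | 15.5% |
| 0.3 | 1.423 | 29.1% |

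The lean is an assumption; nothing in the article informs it. The plan analyses these outcomes with ANCOVA, not a plain t test, so the table shows only the order of effect.

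**6. How much can still be masked.** The Trial status section reports 62 patients included on 5 January 2021, which leaves 110 − 62 = 48 (44%). Suppose, as a best case, that masking starts with the 63rd patient and dropout is even. The 90 evaluable patients then split into 90 × 62/110 = 50.7 and 90 × 48/110 = 39.3, or about 25.4 and 19.6 per arm. The difference between the unmasked and masked treatment contrasts has standard error √(2/25.4 + 2/19.6) = 0.43 SD, so a 95% interval of about ±0.83 SD. A comparison by masking status can be reported, but it could not detect leans of the size in step 5.

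**The case against.** The strongest reply is that little of the trial's confirmatory claim depends on this. The one confirmatory test is on a patient-reported VAS, and the Statistical methods section {20a} calls everything else exploratory, without multiplicity adjustment. A reader might infer that the open examiners compromise the primary result. They do not, and masking them would not reduce the open-label bias in the VAS. Nor does an inflated error rate for NDS or cTNS describe any confirmatory test here. All of this stands, and it limits the weight of the point.

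Second, a reader might treat nerve conduction as if it were a clinician's rating. The article points the other way, since the device returns numeric values. Only a smaller, inferred risk remains in how the measurement is taken or repeated.

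Third, a reader might infer that the allocation is telephoned to the examiner. The text says study physician, who may be an acupuncturist. The sentence about recruiting and treating describes the team jointly, while {18a} says the neurologists give no acupuncture. The route is unproven. The blinding statement still leaves them unmasked whoever takes the call.

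Fourth, masking would be imperfect. Patients may disclose their arm. Blood is released at the foot points in numb feet (Study intervention), and bruising at needle sites is a known effect (Adverse event reporting), so a foot examination at week 8 may reveal treatment. With more than half the patients already included, a change also creates two assessment regimes. These are real costs, but they do not make masking pointless.

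Fifth, the examination schedule is not wholly clear. The Study intervention section has controls followed only by diaries and questionnaires until week 16, and the retention section {18b} counts two follow-up examinations. Study setting and Outcomes, by contrast, describe follow-up examinations of controls and three follow-up time points. The point applies wherever both arms are in fact examined.

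**Conclusion.** The point holds as a risk of bias in secondary outcomes. The stated plan leaves the raters of NDS and cTNS unblinded although they are already separate from treatment, so the risk is avoidable. It falls mainly on the between-arm contrasts at weeks 8 and 16, is smaller for sural nerve conduction, and does not touch the primary VAS.

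A reader might conclude that bias is built into these results. The documents do not show that: they show examiners who may know the arm, not examiners whose ratings lean. The figures of 7.6% to 29.1% illustrate what assumed leans would do and are not estimates for this trial.

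The conclusion assumes that the neurologists count among the physicians aware of allocation, and that both arms are examined at weeks 8 and 16. If the neurologists are masked in practice, sections {17a}, {17b} and {11a} misdescribe the trial and still need correction. The change is worth making because it is cheap and because any conclusion about nerve regeneration would need these measurements. It is not a condition for the validity of the primary analysis.

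**What to change.** 1. Amend {17a} and {17b} so that the two neurologists are masked assessors of NDS, cTNS and nerve conduction at all remaining follow-up examinations.
2. In {16b} and {16c}, have the coordinating nurse, who already generates the allocation, give it to a treating acupuncturist and not to the examining neurologist. Someone other than the neurologist informs the patient.
3. Keep treatment records out of the examination file, ask patients not to disclose their arm, and record any unmasking at each examination.
4. Reconcile the team description in {11a} with {18a}, and state at which weeks each arm is examined.
5. Report which examinations were done before masking, and add a sensitivity analysis of NDS and cTNS by masking status. Present it with confidence intervals and without weight on a test, given the ±0.83 SD in step 6.

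Cost: no extra staff, only a rerouted call, a patient instruction, one field on the examination form and an amendment. Masking will be incomplete because of disclosure and visible needle or bloodletting marks, and the trial will contain two assessment regimes. For patients already included, a neurologist who knows the arm cannot be masked retrospectively.
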